**Methods/design:**

Three cohort studies - the Kimberley Healthy Adults Project (KHAP, *N* = 363), Koori Growing Old Well Study (KGOWS, *N* = 336) and Torres Strait Dementia Prevalence Study (TSDPS, *N* = 274) - share a similar research methodology with demographic, medical history, psychosocial factors, cognitive tests and consensus clinical diagnoses of cognitive impairment and dementia. Associations between risk and protective factors of interest and the presence of dementia and/or cognitive impairment diagnoses will be evaluated by univariable and multivariable logistic regression in a harmonised cross-sectional cohort of 898 participants. Factors associated with incident dementia and/or cognitive impairment will be assessed in a subset of KHAP (*n* = 189) and KGOWS participants (*n* = 165) who were available in longitudinal follow-up, after exclusion of those with baseline dementia or cognitive impairment. Analyses in relation to outcome measure of death or dementia will be conducted to account for the competing risk of death. Logistic regression will be used to evaluate the association between the individual components of the 16-component Kimberley Indigenous Cognitive Assessment (KICA) tool and the presence of dementia and cognitive impairment determined by independent consensus diagnoses. Multivariable binary logistic regression will be used to adjust for the effect of confounding variables. Results will be reported as odds ratios (OR) with 95% confidence intervals (95% CI).

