Three landmark Australian studies involving Aboriginal and Torres Strait Islander cohorts from Western Australia (WA), New South Wales (NSW), and the Torres Strait in Far North Queensland have researched factors associated with dementia. In a cross-sectional study of 363 Aboriginal people aged 45 years and older living in the remote Kimberley region of WA, dementia was associated with smoking, stroke, epilepsy, head trauma, poor mobility, incontinence and falls, after adjustment for age, sex and education. On follow-up, only age and head trauma endured as longitudinal risk factors for cognitive decline [8, 9]. In a cohort of 336 participants in the major city of Sydney and regional NSW, multivariable analysis highlighted age, childhood trauma, unskilled work, stroke and head injury as independent predictors of all-cause dementia alongside comorbid factors such as depression, current high risk alcohol use, low Body Mass Index (BMI), mobility impairment, functional impairment, incontinence, hospitalization in the past year, residing in residential care, social isolation and low physical activity levels [2, 10]. Older age, male sex, unskilled work history, and polypharmacy were associated with incident dementia and Mild Cognitive Impairment (MCI) [11]. On follow-up, age, male sex, unskilled work, polypharmacy and Apolipoprotein E allele 4 (APOE ε4) were longitudinal risk factors for cognitive decline. However, similar to the Kimberley study, the competing risk of mortality was not taken into consideration, which likely impacted these longitudinal results [9]. In the Torres Strait, cerebrovascular disease, chronic kidney disease, and older age were significantly associated with dementia in a cohort of 274 participants [12]. Vascular risk factors other than stroke, such as diabetes and hypertension, were not associated with dementia in any of the cohorts, possibly due to the ubiquity of these conditions, non-linear risk relationships or limited statistical power. This is consistent with the findings of a recent systematic review that highlighted the limited data on risk factors for vascular dementia and a lack of geographical representation for many risk factors for dementia [13].

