## Methods/design

### Design

The KHAP study was undertaken from 2004 to 2006 and involved 363 Aboriginal participants aged 45 and older from different communities in the remote Kimberley region of WA [1]. The KGOW study recruited 336 participants aged 60 and older from five Aboriginal communities, two from metropolitan Sydney and three in regional coastal areas of NSW between 2010 and 2012 [14]. Follow-up of participants occurred after six and seven years for KGOWS-II and KHAP wave 2, respectively. The TSDP study was conducted between 2015 and 2018 and recruited 274 participants aged 45 and older from five mainland and 18 island communities across the Torres Strait and Northern Peninsula [3]. A summary of the studies and number of participants is provided in Table 1. All three cohort studies worked in partnership with local community organisations and Aboriginal and Torres Strait Islander members and researchers to support recruitment, data collection, and feedback to communities to ensure culturally safe engagement with participants. Risk factors were collected using a structured interview protocol and encompassed demographic, medical, and psychosocial factors collected from participants and family carers where available. This comprehensive assessment was independently evaluated by a panel of clinical specialists to establish clinical diagnoses by consensus. All three cohort studies used the KICA, a screening tool for older Aboriginal and Torres Strait Islander peoples, that was validated in the remote Kimberley region of WA [15], modified for urban and regional dwellers in the form of the mKICA [16] and adapted for the Torres Strait [17]. A shortened version (KICA-Screen) has been validated for face-to-face and telehealth administration [17, 18].

**Table 1 Tab1:** Descriptive summary of landmark studies

Study/Cohort	Location	Age (years)	Sample Size (*N*=)	Participants (*n*=)
Kimberley Healthy Adults Project (KHAP)				
Wave 1 (W1) 2004–2006 [1, 8]	Remote WA	≥ 45	363	289 with normal cognition; 45 with dementia; 29 with CIND*.
Wave 2 (W2) 2011–2013 [9]	Remote WA	≥ 45	398‡	. Of 363 W1 participants, 184 completed all W2 assessments, 5 had cognitive assessment only, 109 had died and 65 declined to participate or could not be located. 105 new participants were recruited at W2. W2 cohort: 226 with normal cognition; 29 with dementia; 33 with CIND; 1 missing diagnosis; had 109 died.
Koori Growing Old Well Study (KGOWS)				

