#### Data analyses

Data will be analysed using the Stata statistical package (StataCorp, College Station, Texas), version 17. Analyses will be performed on harmonised cross-sectional and longitudinal data. Associations between risk and protective factors of interest and the presence of dementia and/or cognitive impairment based on consensus diagnoses will be evaluated by univariable and multivariable binary logistic regression. Analyses by dementia subtype will also be conducted to ascertain risk factors of importance between groups. In the longitudinal cohort, risk factors of interest will be determined from baseline measures (W1), compared with consensus diagnoses at follow-up (wave 2) and analysed in relation to outcome measures of incident dementia and/or cognitive impairment using univariable and multivariable logistic regression. To account for the competing interest of death (*n* = 177 before wave 2 follow-up), multinominal logistic regression will be used to estimate the association between variables of interest and the following outcomes: (1) neither cognitive impairment nor dementia nor died; (2) cognitive impairment or dementia during the study; and (3) death between baseline and follow-up. Results will be reported as odds ratios (OR) with 95% confidence intervals (95% CI). Multivariable binary logistic regression will be used to adjust for the effect of confounding variables that are anticipated to be associated with dementia such as age, sex, education and study cohort. Variables that are significant in univariable analyses will be entered into a multivariable model, after which a process of clinical judgement and examination of measures including the Akaike and Bayesian information criteria will be employed to decide which variables to retain in the final multivariable model.

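### The three-outcome multinomial model adds an odds ratio for death, but its impairment odds ratio is still the survivors-only one and is not corrected for the competing risk

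*Protocol article*

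**What the plan says.** The second primary outcome (Study aims) concerns factors associated with incident dementia or cognitive impairment in the pooled longitudinal data. Under Data analyses, wave 1 factors are first related to wave 2 consensus diagnoses by binary logistic regression.

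A second model is then added. Its purpose is stated as "To account for the competing interest of death", with the number of deaths given as "177 before wave 2 follow-up". The method is that "multinominal logistic regression will be used to estimate the association between variables of interest and the following outcomes", namely "1) neither cognitive impairment nor dementia nor died; (2) cognitive impairment or dementia during the study; and (3) death between baseline and follow-up". The only measure named for the results is the odds ratio with its 95% confidence interval.

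Two other places bear on this:

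- The Background says of the earlier Kimberley and New South Wales follow-up analyses that "the competing risk of mortality was not taken into consideration, which likely impacted these longitudinal results".
- The abstract describes the competing-risk analysis differently: "Analyses in relation to outcome measure of death or dementia will be conducted to account for the competing risk of death".

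**The concern.** The plan presents the multinomial model as its answer to a fault it finds in earlier work. A reader will expect its impairment odds ratio to be the one that takes mortality into account. But a multinomial logit compares each outcome with a reference outcome, and the comparison of impaired with unimpaired does not involve the people who died.

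This affects one of two primary outcomes, and deaths are numerous: half as many as the people followed up. If the binary and multinomial impairment odds ratios agree, as they must apart from estimation noise, the agreement could be taken as evidence that mortality does not matter. It would show nothing of the kind.

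The label of the second outcome adds to the problem. It refers to the whole study period, yet a person who became impaired and died before wave 2 is counted under death.

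**Working it through.** **Inputs, all from Table 1 and the Data harmonisation and Data analyses sections**

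- KHAP: "184 completed all W2 assessments, 5 had cognitive assessment only", so 184 + 5 = 189 followed up; "109 had died and 65 declined to participate or could not be located".
- KGOWS: 165 followed up, 68 died, 103 did not participate.

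**The plan's own figures**

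- Deaths: 109 + 68 = 177, as stated.
- Followed up: 189 + 165 = 354, as stated.
- Deaths as a share of those with a known outcome: 177 / (354 + 177) = 177/531 = one third.

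These counts cover wave 1 participants in general. The 165 in KGOWS include 10 with dementia at baseline, so the numbers at risk of incident impairment are somewhat smaller. The argument does not depend on this.

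**The identity**

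Code the outcomes 1 (unimpaired), 2 (impaired or demented) and 3 (died).

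- Multinomial model: log[P(2|x) / P(1|x)] = a2 + b2·x.
- Binary model in those followed up: log[P(2|x, not 3) / P(1|x, not 3)].
- Since P(k|x, not 3) = P(k|x) / P(not 3|x) for k = 1, 2, the factor P(not 3|x) cancels from the ratio.

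The slope in both models is therefore b2. The choice of base category is immaterial, because the contrast of 2 with 1 is the same under any base.

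The identity applies because outcomes 1 and 2 are both survivors: the diagnosis is made at wave 2, Table 1 counts deaths apart from wave 2 diagnoses, and no diagnosis between waves is described.

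**Illustration with the plan's totals**

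The split by exposure is assumed. Survivors are held fixed at 170 unimpaired and 40 impaired (unexposed), and 106 and 38 (exposed), which sum to 354. The 177 deaths are divided in three ways.

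- Impaired versus unimpaired: OR = (170 × 38) / (40 × 106) = 6460/4240 = 1.52.
- SE of log OR = √(1/170 + 1/40 + 1/106 + 1/38) = 0.258.

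The fitted multinomial and survivors-only models both returned 1.5236 (SE 0.2581) for every split.

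| Deaths, unexposed / exposed | Impaired vs unimpaired, either model | Death vs unimpaired | Impaired vs everyone else | Impaired or died vs unimpaired | Probability of impairment, unexposed / exposed |
|---|---|---|---|---|---|
| 55 / 122 | 1.52 | 3.56 | 0.94 | 2.70 | 40/265 = 0.151; 38/266 = 0.143 |
| 88 / 89 | 1.52 | 1.62 | 1.26 | 1.59 | 40/298 = 0.134; 38/233 = 0.163 |
| 137 / 40 | 1.52 | 0.47 | 2.00 | 0.71 | 40/347 = 0.115; 38/184 = 0.207 |

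Only the impairment odds ratio ignores where the deaths fall.

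**With continuous covariates**

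The parameter is still the same, but the two estimates need not be identical. In 400 simulated data sets of 531 people (assumed conditional odds ratios of 2 for impairment and 3 for death, with a shared unmeasured frailty), the geometric mean odds ratios were 1.420 (multinomial) and 1.426 (binary). Their correlation was 0.994, and the mean absolute difference in log odds ratio was 0.026 against a standard deviation of 0.30. The same covariate model fitted to everyone's impairment status, including those who died, gave 1.83. Under these assumptions, both planned models moved toward 1 by almost the same amount.

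**The case against.** The strongest reply is that the model does something useful with the deaths. It places an odds ratio for death beside the one for impairment, so a reader can see whether a factor is linked to one, the other or both. With two waves and no event times described, modelling each event type separately is a recognisable approach. Its fitted probabilities also keep the deaths in the denominator. All of this stands. A reader might infer that the multinomial model is worthless or should be dropped, and the documents do not support that. The fault is confined to what the impairment odds ratio is taken to mean.

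It can also be said that marginal effects are a reporting detail for the registered analysis plan, which is not shown. That is fair as to the command used. But the article itself fixes the purpose, the model, the outcomes and odds ratios as the measure, and the purpose is not met by the impairment odds ratio.

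A reader might infer that the abstract commits the study to a composite endpoint and so contradicts the methods. Its phrase does read as a composite, but that word is not used, and it may be a compressed account of the three outcomes. The wording is ambiguous and needs reconciling; more than that cannot be claimed.

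Lastly, measures that use the deaths are not simply better. Probabilities with deaths in the denominator mix effects on impairment with effects on death, and a composite brings in predictors of mortality. Neither recovers impairment that arose before death.

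**Conclusion.** The concern holds in this limited form: the outcome 2 versus outcome 1 odds ratio is conditional on being alive at wave 2 and equals, as a parameter, the survivors-only binary odds ratio. Adding death as a category supplies a separate death odds ratio and leaves the impairment odds ratio uncorrected. This is algebra. It rests on two conditions: impairment is ascertained only at wave 2, as the article describes, and the two models use the same covariates.

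The practical size is not fixed by the documents. A reader might infer that conclusions would reverse, or that about half of dementia cases are hidden among the deaths. Both follow only from particular assumptions. In simulations where the exposure raised the dementia hazard 1.5-fold and the death hazard 2-fold, with mortality 2.5 times higher after onset, the odds ratio counting deaths as non-events was 0.82 to 0.89, and 42 to 56% of dementia cases died before wave 2. With a death hazard ratio of 1.3, mortality 1.5 times higher after onset and no frailty, the multinomial odds ratio was 1.52 against 1.34 with deaths as non-events, and 22% of cases died before wave 2. With no effect on death and no extra mortality, the figures were 1.59, 1.55 and 14%. These are illustrations.

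The cross-sectional primary analysis of 898 participants is unaffected.

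**What to change.** 1. From the same multinomial model, also report covariate effects on the absolute probabilities of outcomes 2 and 3 (average marginal effects), beside the two odds ratios. The denominator should be everyone at risk at baseline, including those who died. The 65 + 103 = 168 who declined, could not be located or did not participate have no observed wave 2 outcome, and the report should say so.
2. State that the outcome 2 odds ratio is conditional on being alive at wave 2 and does not by itself account for death, and that its agreement with the binary model is not evidence of robustness to mortality.
3. Relabel outcome 2 as impairment or dementia diagnosed at wave 2, and outcome 3 as died before wave 2 with cognitive status at death unknown.
4. Reconcile the abstract with Data analyses. If a composite is intended, define it and report it as a separate question.

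The cost is two post-estimation commands in Stata, one further logistic model if a composite is wanted, and some rewording. No new data are needed. The absolute-probability effects mix impairment with mortality, so they should supplement the odds ratios and not replace them.

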#### Variables of interest

Risk and protective variables of interest associated with dementia are derived from the 2020 Lancet report, the World Health Organisation (WHO) guidelines, Cardiovascular Risk Factors Aging, and Incidence of Dementia (CAIDE) index, and Australian National University Alzheimer’s Disease Risk Index (ANU-ADRI) and summarised in Table 2. These are life-course risk and protective factors for dementia in the general population and well established in the literature [13, 25–27]. We have included these measures for analysis across the three studies to establish whether the same risk factors are relevant to Aboriginal and Torres Strait peoples. Studies have also shown that certain syndromes such as falls, executive dysfunction, depressive symptoms and urinary incontinence may be more common in older people with cerebral white matter changes suggestive of cognitive vulnerability and impairment [28, 29]. Measures of mobility impairment, falls, sleep disturbance, urinary incontinence, and impairments in ADLs will be included to look at these syndromes. Additionally, history of cardiovascular, renal, or cerebrovascular disease inclusive of stroke or a transient ischaemic attack are included as markers of vascular comorbid conditions.

**Table 2 Tab2:** Compilation of risk factors of interest based on existing literature

Measure	Data available
Less education (< 10 years) *†‡§	Simple measure in KHAP W1. Levels of education available in KHAP W2, KGOWS and TSDPS.
Hearing impairment*	Yes
Physical inactivity/exercise *†§	Simple measure available in KGOWS but not in KHAP or TSDPS
Cognitive stimulation †§	Skilled work/jobs as a proxy measure in KGOWS only
Head injury with loss of consciousness *§	Yes
Diabetes †*§	Yes
Hyperlipidaemia/ high cholesterol †‡	KHAP W2, KGOWS and TSDPS only
Hypertension *†‡	Yes
Infrequent social contact/social isolation *†§	Only available from KGOWS data Subjective loneliness, living alone, social activity participation in prior 3 months for 10 activities
Diet (e.g. fish intake) †§	No
Alcohol consumption *†§	Yes
Air pollution *	No
Smoking *†§	Yes
Obesity (Body mass index > 30) †*‡	Only in KHAP W2 and KGOWS
Depression/Depressive symptoms *†§	Yes
Older Age ‡§	Yes
Sex §	Yes

* Dementia prevention, intervention, and care: 2020 report of the *Lancet* Commission [26]

†World Health Organisation (WHO) guidelines [30]

‡ Cardiovascular Risk Factors Aging, and Incidence of Dementia (CAIDE) Risk Score [31]

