#### Data harmonisation

Data will be harmonised using the Stata statistical package (StataCorp, College Station, Texas), version 17. Variables of interest will be recoded to be consistent across datasets prior to combination into a single final dataset. Data harmonisation utilises the best available information. This means that patient self-reports for a given variable may be corroborated by information from family reports, medications, primary care software derived medical history and medications where available. For instance, the variable diabetes combines self-reports of the condition (yes/no), family informant reports of the condition (yes/no), and medication history (diabetic medication by self-reports or in medication review). Medication lists available for the participants will be coded using the World Health Organization’s Anatomical Therapeutic Chemical (ATC) Classification and allow for sub-analyses of outcomes in relation to medication categories of interest such as anticholinergics, analgesics, anti-psychotics and so forth [33]. The full details of variables of interest in the pooled cross-sectional dataset are provided in the appendices (Appendix 1.1).

Based on the variables of interest available in each dataset (Table 2), KHAP wave 2, KGOWS-I and TSDPS will be harmonised in cross-section, with a combined cohort of 898 Aboriginal and Torres Strait Islander participants, 244 (27%) of whom will have a diagnosis of dementia or CIND/MCI. For longitudinal analyses, data from KHAP wave 1 will be harmonised with KGOWS-I and combined with diagnoses at baseline (wave 1) and follow-up (wave 2) for analysis of factors of interest in a smaller subset of 354 participants as summarised in the appendices (Appendix 1.2). There is no longitudinal data available for TSDPS at the present time.

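### Unadjusted univariable significance decides which factors reach the multivariable model, so a factor inversely related to age or cohort can be screened out despite a real adjusted association

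*Protocol article*

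**What the plan says.** The protocol article, Data analyses, sets two steps. For entry: "Variables that are significant in univariable analyses will be entered into a multivariable model". For retention: "clinical judgement and examination of measures including the Akaike and Bayesian information criteria will be employed to decide which variables to retain" in the final model. The sentence just before the entry rule says that multivariable logistic regression will adjust for "confounding variables that are anticipated to be associated with dementia such as age, sex, education and study cohort". The univariable screen carries no such adjustment.

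The cross-sectional pool, under Data harmonisation, is a "combined cohort of 898 Aboriginal and Torres Strait Islander participants, 244 (27%) of whom will have a diagnosis of dementia or CIND/MCI". Table 1 gives a minimum age of 60 for KGOWS and 45 for KHAP and TSDPS.

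Table 2 lists obesity as available "Only in KHAP W2 and KGOWS", so it is absent for all of TSDPS and for KHAP wave 1. Hyperlipidaemia is present in all three cross-sectional datasets but not in KHAP wave 1, which is part of the longitudinal baseline. Under Missing data and outliers, imputation is an option once more than 5% of a variable is missing.

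**The concern.** The plan recognises that age, sex, education and cohort confound these associations, yet it chooses candidates on estimates that ignore them. Age is expected to be a strong determinant of impairment, and the pool mixes cohorts with different age floors and outcome rates. A crude odds ratio for a factor that declines with age is pulled towards 1 or below it, so a harmful factor can miss significance and never be examined with adjustment. Finding risk and protective factors is the primary aim, and greater statistical power is a stated reason for pooling. A false null created by the screen works against both.

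A second, conditional issue concerns retention. AIC and BIC depend on the participants in the model. If a variable that one cohort never collected enters a complete-case model, the sample shrinks and the criteria no longer measure the same thing.

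**Working it through.** **1. The plan's own totals.** KHAP wave 2 has "226 with normal cognition; 29 with dementia; 33 with CIND; 1 missing diagnosis", so 226 + 29 + 33 = 288 people with a diagnosis.

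- N = 288 + 336 + 274 = 898.
- Impaired = (29 + 33) + (45 + 38) + (39 + 60) = 62 + 83 + 99 = 244, and 244/898 = 27.2%.

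Both stated figures reproduce. Impairment by cohort is 62/288 = 21.5%, 83/336 = 24.7% and 99/274 = 36.1%.

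**2. What the crude screen does.** The article gives no age distribution, no factor-by-age gradient and no alpha for the screen, so all of these are assumed:

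- cohort sizes 288, 336 and 274 with minimum ages 45, 60 and 45 (from the article);
- age above the minimum drawn from a gamma distribution (shape 2.2, scale 7 years), capped at 100;
- exposure log-odds of -0.4 at age 66, changing linearly with age;
- overall impairment 244/898, with no cohort effect beyond age;
- true OR 1.6, two-sided alpha 0.05, and 1000 runs per row (Monte Carlo standard error at most about 1.6 percentage points).

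The adjusted model contains the factor, age and cohort.

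| Age effect, OR per 10 years | Factor-age OR per 10 years | Mean crude OR | Crude screen passes | Adjusted test detects |
|---|---|---|---|---|
| 1.5 | 1.00 | 1.565 | 84.0% | 85.8% |
| 1.5 | 0.74 | 1.312 | 45.0% | 85.4% |
| 1.5 | 0.61 | 1.186 | 20.5% | 81.0% |
| 2.0 | 1.00 | 1.506 | 78.1% | 82.9% |
| 2.0 | 0.74 | 1.135 | 15.2% | 80.6% |
| 2.0 | 0.61 | 0.966 | 6.3% | 77.7% |
| 2.5 | 1.00 | 1.454 | 70.9% | 78.9% |
| 2.5 | 0.74 | 1.008 | 5.3% | 74.3% |
| 2.5 | 0.61 | 0.833 | 23.0% | 74.4% |

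Factor-age ORs of 0.74 and 0.61 are slopes of -0.3 and -0.5 log-odds per decade. In the last row the mean crude OR is below 1, so the passes are in the wrong direction. A separate 400-run batch that counted only significant results in the right direction had none.

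**3. Sensitivity to the assumptions.** Other assumed age distributions and exposure prevalences gave, crude against adjusted:

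- slope -0.6, age OR 2.2: 6% to 10% against about 77%;
- slope -0.4, age OR 1.5: 58% to 61% against 83% to 87%;
- slope -0.1, age OR 2.2: 64% to 68% against 81% to 83%;
- slope +0.2, age OR 2.2: 94% to 95% against 82% to 86%.

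The loss therefore runs from large to almost nil, and reverses once the factor rises with age.

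**4. AIC and BIC on unequal samples (conditional).** Obesity is missing for 274/898 = 30.5%, leaving 624 people and 62 + 83 = 145 cases. The intercept-only deviance is D = -2[e ln(e/n) + (n - e) ln((n - e)/n)].

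- n = 898, e = 244: D = 1050.6; AIC = 1050.6 + 2 = 1052.6; BIC = 1050.6 + ln 898 = 1057.4.
- n = 624, e = 145: D = 676.6. With one added term that explains nothing, AIC = 676.6 + 4 = 680.6 and BIC = 676.6 + 2 ln 624 = 689.4.

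The apparent gain is 1052.6 - 680.6 = 372 in AIC and 1057.4 - 689.4 = 368 in BIC. On the same 624 people the useless term raises AIC from 678.6 to 680.6, as it should. In the longitudinal pool, obesity and hyperlipidaemia are absent for the KHAP part, 189/354 = 53.4%.

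**The case against.** The article reports univariable associations, names its confounders, tempers retention with clinical judgement and disclaims causal inference from the cross-section. Its confounder sentence could mean that every factor gets an adjusted odds ratio whatever the screen shows. If so, that sentence and the entry rule conflict and need reconciling. As printed, the entry rule is explicit, so the main point stands.

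Several stronger readings are tempting but unsupported:

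- **That named factors will be lost.** Masking needs an inverse link with age or cohort. The article gives no such gradient for smoking, alcohol, obesity or anything else.
- **That the screen would perpetuate the source studies' null vascular findings.** The article names diabetes and hypertension. Nothing in it shows either declining with age, and factors that rise with age pass more often.
- **That age-related bystanders become false findings.** A null factor rising by 0.6 log-odds per decade passed the screen in 59% or 91% of runs, depending on the assumed ages. It then meets an age-adjusted model, where it was significant in only 3% to 6%.
- **That AIC and BIC will be compared across unequal samples, or that obesity must be imputed for all of TSDPS.** The article says neither. Imputation is optional, and a variable can simply be left out of the three-cohort model. The variable list is in an appendix and the registered analysis plan is not shown. Only the conditional point survives.

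**Conclusion.** The point holds for the stated entry rule. Screening on unadjusted significance, next to a list of confounders that the screen ignores, can remove a factor with a real adjusted association. The size rests wholly on assumed inputs: with true OR 1.6 and exposure falling 0.3 to 0.6 log-odds per decade, about 5% to 60% pass the crude screen against about 74% to 87% detected after adjustment. The simulations show masking by age only; they add no separate cohort effect and do not model sex or education. They establish that the loss can be serious, not that it will occur for any particular factor.

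The AIC and BIC point is conditional on variables that a whole cohort lacks entering complete-case models. Obesity in the cross-section is the clearest case, because the Discussion does not list it among the acknowledged omissions, unlike physical inactivity, cognitive stimulation and social isolation. The change should be made before the analysis, since a selection rule is hard to repair credibly once results are known.

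**What to change.** Remove the univariable p-value gate. For each candidate factor available in the pooled data, report the odds ratio from a model with age, sex, education and study cohort forced in, whatever its crude p-value. Crude estimates can stay as description. If a reduced model is wanted, choose it from the pre-listed factors with those four covariates always retained.

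State that AIC and BIC are compared only between models fitted to one common set of participants. Analyse a variable that a cohort did not collect separately, in the cohorts that did: obesity in KHAP wave 2 and KGOWS for the cross-section, and obesity and hyperlipidaemia in KGOWS alone for the longitudinal analysis.

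The cost is a change of wording, slightly more reporting and a less parsimonious set of results. No new data are needed. Particular modelling techniques, such as splines for age or penalised likelihood, are a matter of preference and are not required to resolve this point.
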